### Secondary outcome measures

*SCL-90-R.* The Symptom Checklist-90-Revised
^39^ is used to assess a broad spectrum of complaints, such as pain, depression and hopelessness, and with the SCL-90-R, we are able to reliably assess clinically significant change
^40^. Test-retest correlations, for a 10-week interval, were found to range from r = .68 to .80
^41^.

*SDL.* The Sleep Diagnosis List
^42^ is a self-report questionnaire that consists of 75 statements related to sleep and symptoms of sleep disorders. It will be used as a subjective measure of sleep and to control for disorders associated with sleep disturbances. The SDL is based on the Sleep Diagnosis Questionnaire
^43,
44^ and has been validated in a large Dutch population with sleep disorders
^45^.

*PSQI.* The Pittsburgh Sleep Quality Index
^46^ is a commonly used self-report questionnaire and is used to assess e.g. sleep quality and sleep duration. Internal consistency of the PSQI ranges from 0.70 to 0.80 (Cronbach’s alpha) and the PSQI is known to have a good construct validity
^47^; PSQI scores are more highly correlated to sleep disturbances (r = .69 to .77) than to e.g. mood and depression (r = .22 to .65). In patients with primary insomnia, the PSQI has been shown to have a high test-retest reliability, with r = 0.87
^48^.

*AVL.* The Aggression Questionnaire
^49^ is a self-report questionnaire that consists of 29 statements that are related to aggressive thoughts and behaviour. While internal consistency for the global aggression scale and three subcomponents are sufficient (Cronbach’s alpha > 0.7), the internal consistency of the verbal aggression subcomponent is insufficient (Cronbach’s alpha = 0.5). Test-retest correlations for all subcomponents and the total score are high, r > 0.76.

*Activities.* Participants are asked to provide an estimate of their participation in activities such as sports, labour and outdoor time on a 4-point Likert scale (never, sometimes, often, always). In addition, participants are asked to estimate the average hours per day spent on activities such as watching television and reading.

*Demographic and control variables.* At baseline, demographic variables such as age, level of education, type of crime, number of previous incarcerations and current medication use are gathered.

### Statistical analysis

For the main research questions (i.e. does running therapy improve cognition and sleep?), a repeated measures AN(C)OVA will be conducted for the results on the CANTAB and for the various sleep variables, comparing the baseline results with the post-measurement results. The main analyses will be conducted according to the intention-to-treat principle. Missing data will be imputed using the multiple imputation function as provided in SPSS 21 (IBM Corp, Armonk, NY, USA).

### Sample size calculation

A sample size calculation was made using G*Power version 3.1.3
^50^. Since no similar studies have been conducted, the effect size was set small-to-moderate (
*f* = 0.15). The lowest test-retest correlation of one of the used CANTAB tests was used as input for the correlation between repeated measures (r = 0.6).

In sum, effect size was set to
*f* = 0.15, with an alpha error probability of
*p* = 0.05, power of 1-β = 0.8, 1 group, 2 moments of measurement and correlation among repeated measures of r = 0.6. In G*Power, this resulted in a total sample size of N = 72.

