## Abstract

**Background: **Executive dysfunction appears to be related to increased recidivism. Of note is that sleep disturbances, which are highly prevalent in prisons, may attenuate executive functions. Thus, improving executive functions, either directly or indirectly through the improvement of sleep, may reduce recidivism. It is hypothesised that physical exercise, in the form of Running Therapy, has a direct positive effect on executive functions as well as an indirect effect through the improvement of sleep.

**Methods/Design: **Seventy two (N = 72) detainees in various penitentiary institutions in the Netherlands will be recruited in this study. A baseline measurement, including six neuropsychological tests of the Cambridge Neuropsychological Test Automated Battery (CANTAB), an assessment of sleep quality and duration using the Actiwatch (Actiwatch 2, Philips Respironics, Murrysville, PA, USA) and various other measurements will be administered before the start of the treatment. After 3 months of Running Therapy, participants will be assessed again with the same tests for neuropsychological and physical functioning. Primary outcomes are executive functioning and various sleep variables.

**Discussion: **This study will be the first to investigate the possible influence of Running Therapy on the cognitive functioning, sleep and aggression in prisoners.

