### Participants

Prisoners (male adults) of two Penitentiary Institutions in the Netherlands (i.e. PI Leeuwarden and PI Ter Apel) that are referred to Running Therapy by the psycho-medical staff will be recruited in this study. Various complaints or disorders may result in referral to Running Therapy, e.g. ADHD, sleep disturbances, anxiety disorders and depression. All participants in Running Therapy who speak sufficient Dutch or English will be approached and asked to participate in this study. In addition, we will attempt to approach those who do not speak Dutch or English by using a translation phone service often used in Penitentiary Institutions by the psycho-medical staff. As we are not allowed to interfere with daily practice in prison, participants will continue to receive treatment-as-usual from the prison care, which may entail changes in drug regimen or participation in other interventions. Participants may be excluded from Running Therapy when they sustain an injury or when they behave aggressively. Such decisions are made by the running therapist in concordance with the prison staff.

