Studying an intervention such as Running Therapy in prison comes with challenges and considerable limitations. One such limitation is that it we will be conducting a Phase I/II study instead of an RCT, as the participating prisons were not ready to directly allow an RCT. A follow-up RCT would be needed to confirm any positive results. Another limitation is that rewards for participation are not allowed, making it more challenging for us to recruit participants. An example of a logistic issue is the difficulty in planning a meeting with a participant with sufficient time to administer all the tests and questionnaires. Our solution is to ask participants to fill out a number of the questionnaires in their own time and bring these with them to therapy a week later, which might result in a somewhat lower compliance rate for these questionnaires. Another limitation concerns the use of actigraphy to measure sleep. Polysomnography is considered the gold standard in sleep research, with actigraphy being the second most valid method. However, as it not within our possibilities to temporarily transport all the participants to a sleep research lab for polysomnographic research, for this study, we consider actigraphy to be the most suitable and valid method; a clear advantage of actigraphy is the possibility to study the participants in the environment they reside in. One limitation of actigraphy is that we know from previous experience in prison, a number of the participants choose not to wear the Actiwatch, as they fear it might affect their social status with their fellow inmates. These limitations are examples of the challenges one faces when conducting research in a prison environment. In our view, however, prisoners are an important population with great impact on society, and researchers should not be discouraged to conduct research in this setting. Instead, we should try to build expertise conducting research in this particular environment, and hopefully, the results of our study will help to pave the way to the possibility to conduct RCTs in prison in the future.

In sum, if the results are indeed in accordance with our hypotheses, Running Therapy may eventually prove to be a useful approach to improve executive function, and possibly reduce aggressive behaviour and psychiatric symptoms of depression, ADHD, sleep disturbances and anxiety in prisoners.

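### N = 72 is the number of complete before-after pairs that 80% power requires, but it is also the number recruited; with an optional Actiwatch that some decline, the stated power does not hold for sleep

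*Protocol article*

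**What the plan says.** The section Sample size calculation lists its inputs in full: effect size f = 0.15, alpha 0.05, and "power of 1-β = 0.8, 1 group, 2 moments of measurement and correlation among repeated measures of r = 0.6". It concludes that "this resulted in a total sample size of N = 72". No allowance for loss is among the inputs.

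The Abstract uses the same number as the recruitment target: "Seventy two (N = 72) detainees in various penitentiary institutions in the Netherlands will be recruited in this study".

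Executive functioning (CANTAB) and sleep are both primary outcomes. Under Measurements and procedures, the Actiwatch is offered as an option and is worn for seven days at baseline and again after three months. The Discussion reports from earlier experience in prison that "a number of the participants choose not to wear the Actiwatch", because of worries about standing among fellow inmates. No rate is given.

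The Participants section says: "Participants may be excluded from Running Therapy when they sustain an injury or when they behave aggressively". The Statistical analysis section plans an intention-to-treat analysis with multiple imputation of missing data.

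**The concern.** In a one-group, two-occasion calculation, N counts people who contribute both measurements. If the same N is the number enrolled, the stated power applies only when nothing is lost. For the Actiwatch, the article itself says that some participants will decline.

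What is at stake is how the results are read. A non-significant sleep result from a subset of volunteers would be set against a claimed 80% power that did not apply to that subset. This matters because the authors hope that the study will open the way to a randomised trial.

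**Working it through.** **Inputs from the protocol article.** From Sample size calculation: f = 0.15, alpha = 0.05, target power 0.80, 1 group, m = 2 measurements, r = 0.6. From the Abstract: 72 to be recruited. The rate of incomplete pairs is not given, so it is varied below as an assumption.

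**Formula.** Repeated-measures ANOVA, within factor, one group: noncentral F with

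- λ = f² × N × m / (1 − r)
- df1 = m − 1 = 1
- df2 = (N − 1)(m − 1) = N − 1

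This is equivalent to a two-sided paired t test. The effect in units of the single-occasion SD is d = 2f = 0.30. In units of the SD of the difference it is 0.30 / √(2 × 0.4) = 0.335.

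**Reproducing the plan's figure.**

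- N = 72: λ = 0.0225 × 72 × 2 / 0.4 = 8.10; power 0.8016
- N = 71: λ = 0.0225 × 71 × 2 / 0.4 = 7.99; power 0.7960

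The smallest N that reaches 0.80 is 72, so the published figure is correct. It has no slack, since one lost pair takes power below 0.80.

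**Power if 72 are recruited and some pairs are incomplete** (loss rates assumed):

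| Assumed loss | Complete pairs | λ | Power |
|---|---|---|---|
| 0% | 72 | 8.10 | 0.802 |
| 10% | 65 | 7.31 | 0.759 |
| 20% | 58 | 6.53 | 0.709 |
| 30% | 50 | 5.63 | 0.642 |
| 40% | 43 | 4.84 | 0.575 |
| 50% | 36 | 4.05 | 0.499 |

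**Detectable effect at 80% power** (solving for f, then d = 2f): 72 pairs, f = 0.150, d = 0.30; 58 pairs, f = 0.167, d = 0.33; 43 pairs, f = 0.196, d = 0.39.

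**What imputation can add.** These are complete-pair figures, whereas the planned analysis imputes. Suppose that baseline is observed for all 72 and only the post score is missing, at random, with bivariate normal data and unit variance. In large samples the variance of the estimated mean change is then

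(1 − r²)/n + r²/72 + 1/72 − 2r/72,

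where n is the number of complete pairs. Dividing 2(1 − r) = 0.8 by this variance gives the effective number of pairs:

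- n = 58: 0.64/58 + 0.16/72 = 0.01326; 0.8/0.01326 ≈ 60 pairs; power about 73% instead of 71%
- n = 43: 0.64/43 + 0.16/72 = 0.01711; 0.8/0.01711 ≈ 47 pairs; power about 61% instead of 57%

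The gain is small and does not bring power back to 80%. When a participant wore no Actiwatch on either occasion, there is no baseline recording to impute from and this route adds nothing.

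**The case against.** **CANTAB loss is not documented.** A reader might infer that the protocol expects drop-outs from all primary measurements. It does not say so. The sentence about injury or aggression concerns leaving Running Therapy, and under intention-to-treat such a participant can still be tested at three months. The lower compliance foreseen in the Discussion concerns the questionnaires, which are secondary. The plan to impute shows only that some missing data are foreseen. This stands: for CANTAB the point is conditional.

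**The sizes are assumed.** The article says only that some participants refuse. This also stands. No pair count in the table comes from the protocol, and none should be adopted as the sponsor's expectation.

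**Power depends on r as well as N.** The article describes 0.6 as the lowest test-retest correlation among the CANTAB tests used. With a higher value the shortfall could vanish: 65 pairs at r = 0.65 give 81%, and 58 pairs at r = 0.7 give 83%. A reader might therefore go too far in concluding that the design cannot reach 80% power at all. The documents do not support that; the shortfall holds at the stated inputs. Nor do they establish a margin. The CANTAB description says that correlations exceed 0.6 for most subtests, not all, and at r = 0.5 even 72 pairs give only 71%. No correlation is given for any sleep variable.

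**The study is a pilot, and Actiwatch refusal is openly disclosed.** True, and it lowers the severity. But the article states a formal 80% power, and the disclosed refusal was not carried into that statement.

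**Conclusion.** The point holds, mainly for sleep. At the stated inputs, 72 recruits give 80% power only with 72 complete pairs. The article's own account of an optional device that some participants decline rules this out for Actiwatch sleep. For CANTAB the stated power holds only if every recruit completes both assessments.

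The size for sleep depends on an unknown loss rate. Complete-pair power falls from 76% at an assumed 10% loss to 50% at an assumed 50%, with imputation giving back a few points at most when only the post recording is missing. These figures borrow the CANTAB correlation of 0.6 and the common f = 0.15.

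A reader might take this for a calculation error. It is not one, since 72 reproduces exactly. The fault is a missing allowance for incomplete pairs, which is a sample size and power matter. Severity is moderate: the study is a pilot, and no estimate, test or error rate changes.

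**What to change.** In Sample size calculation, state that 72 participants will be recruited and that 80% power at f = 0.15 and r = 0.6 requires all 72 to provide both measurements.

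Then report power, or the effect detectable with 80% power, separately for CANTAB and for Actiwatch sleep. Base each on the sponsor's own expected number of complete pairs; the earlier prison experience cited in the Discussion is the natural source for the Actiwatch. If no figure is available, give a range that is labelled as assumed. For sleep, say also that r = 0.6 is taken from CANTAB, or replace it with a value for the sleep variables.

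No increase in N is needed, and nothing in recruitment, measurement or treatment changes. The cost is a few sentences and a less favourable stated power for sleep.

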### Ethical and legal considerations

This study protocol has been reviewed by CERCO (Committee of Ethics in studies of Law and Criminology), the ethical committee of the faculty of Law at VU University, which declared it saw no objections to the study. In addition, the accredited medical ethical committee of the VU medical centre provided an official declaration (reference number 2014.399) that this study does not need further medical ethical approval, because of the low burden and non-medical non-interventional nature of the study (i.e. the intervention is already part of the institutional care and therefore requires no additional ethical approval). This study has been submitted for registration in the Dutch Trial Register (Nederlands Trial Register); the identification number will be made available in a revised version of this article.

Information letters and Informed Consent forms will be translated in various languages, to ensure that participants can read them in their own language. Data will be coded using a chronological number in combination with an identifier for the institution; the first participant in PI Ter Apel, for example, will be coded as “TA_001”. All non-anonymous data, such as the Informed Consent forms will be stored in the Penitentiary Institutions, as required by the regulations of the Custodial Institutions Agency (DJI). Anonymous data will be stored and analysed at the VU University Amsterdam. Any researcher who works with the participants (i.e. any researcher who could violate the privacy of the participants) is obliged to sign a confidentiality agreement, as required by the regulations of DJI. Students of VU University who will work on this dataset, for example for a thesis project, are required to sign a confidentiality agreement provided by VU University.

### Access to data

The researchers of this study, as well as their students working on this project, will have unlimited access to the dataset. The dataset will be made available to colleagues and peer-reviewers upon request; official approval of DJI may be required beforehand. Variables containing sensitive information may be removed before sharing the dataset, such as date of birth. Participants will not be allowed to see the final data.

### Dissemination

This study will be finished in the second half of 2016, and the results will be published in international peer reviewed scientific journals.

## Discussion

The main purpose of this study will be to investigate the influence of Running Therapy on executive functioning, sleep and aggression of prisoners. To our knowledge, this will be the first study of its kind in a prison population, which may provide results that are relevant to prison administrations, policymakers, and prison clinicians.

Different aspects of Running Therapy may have a positive influence on the prisoner population. Firstly, regular exercise may positively influence executive functions, in particular impulse control
^13,
14^, which could be of importance in reducing recidivism. Secondly, acute bouts of exercise may also improve executive functions such as attention, memory, reasoning and planning
^15,
51^, also making Running Therapy of added value in the short term. For example, it may be useful to plan Running Therapy sessions right before other activities or therapy sessions to improve attentional performance and increase participation of the prisoners. Furthermore, although investigating the influence of Running Therapy on depressive symptoms is a secondary objective of the current study, Running Therapy may have significant clinical impact on these symptoms as well. In general, aerobic exercise has a small-to-moderate effect on depressive symptoms
^32,
52^, which could improve cognition, sleep, and general well-being.

As antisocial personality disorder is highly prevalent in prison (65%)
^53^, this study may also be the first to examine the effects of exercise on the cognition of people with antisocial personality disorder. As impulsivity and/or failure to plan ahead is a clinical hallmark of these patients
^54^, improving executive functions such as impulse control or planning may be of added value in treatment.

Studying an intervention such as Running Therapy in prison comes with challenges and considerable limitations. One such limitation is that it we will be conducting a Phase I/II study instead of an RCT, as the participating prisons were not ready to directly allow an RCT. A follow-up RCT would be needed to confirm any positive results. Another limitation is that rewards for participation are not allowed, making it more challenging for us to recruit participants. An example of a logistic issue is the difficulty in planning a meeting with a participant with sufficient time to administer all the tests and questionnaires. Our solution is to ask participants to fill out a number of the questionnaires in their own time and bring these with them to therapy a week later, which might result in a somewhat lower compliance rate for these questionnaires. Another limitation concerns the use of actigraphy to measure sleep. Polysomnography is considered the gold standard in sleep research, with actigraphy being the second most valid method. However, as it not within our possibilities to temporarily transport all the participants to a sleep research lab for polysomnographic research, for this study, we consider actigraphy to be the most suitable and valid method; a clear advantage of actigraphy is the possibility to study the participants in the environment they reside in. One limitation of actigraphy is that we know from previous experience in prison, a number of the participants choose not to wear the Actiwatch, as they fear it might affect their social status with their fellow inmates. These limitations are examples of the challenges one faces when conducting research in a prison environment. In our view, however, prisoners are an important population with great impact on society, and researchers should not be discouraged to conduct research in this setting. Instead, we should try to build expertise conducting research in this particular environment, and hopefully, the results of our study will help to pave the way to the possibility to conduct RCTs in prison in the future.

In sum, if the results are indeed in accordance with our hypotheses, Running Therapy may eventually prove to be a useful approach to improve executive function, and possibly reduce aggressive behaviour and psychiatric symptoms of depression, ADHD, sleep disturbances and anxiety in prisoners.
